### Recruitment of participants

This study will apply purposive sampling for the recruitment of participants. Participants will be included if they:
Are diagnosed with symptomatic knee OA as defined by the American College of Rheumatology’s Clinical Criteria for Classification and Reporting of knee OA [22–24]Are diagnosed with Grade I and II knee OA based on the Kellgren-Lawrence severity scale [25]Are femaleAge 50 and olderHave body mass index (BMI) between 18.5 and 29.9 kg/m^2^Have knee pain ≥ two on a VAS

Participants with the following conditions will be excluded:
Electrical devices implantNeurological disorders (i.e., stroke)Wheelchair boundSignificant cognitive impairmentPresent systemic inflammatory arthritis (i.e., gout)History of hip or knee arthroplastyHistory of trauma or surgical arthroscopy of either knee in the last 6 monthsReceived knee intra-articular injection within the last 3 monthsUnder anticoagulant therapy, recent or imminent surgery (within 3 months)Involved in any study related to exercise program within the last 6 months

In addition, eligible participants will be considered as drop-outs if they request to withdraw due to any reasons or if they are unable to complete 75% of the intervention program.

### Procedure

Potential participants will first undergo general screening and radiographic screening by the orthopedic medical officer. Disease severity will be assessed using the Kellgren-Lawrence grading system. Pre- and post-intervention assessments will be conducted by the assessors who are blinded to group allocation. These assessments (Fig. 1) will be completed at the sports science laboratory at Universiti Sains Malaysia (USM). All participants will visit USM four times over the 8-week intervention. All participants will also receive the usual care provided by Hospital USM during the 8 weeks of the study, including medication such as pain killers and health education on OA.

### Data collection and management

All the data collection sheets, questionnaires, and printed data of the isokinetic strength test will be stored as hard copy, while the biomechanical data of the gait and STS task will be stored as soft copy in a password-protected computer. Both hard and soft copy data will be stored in a locked room for maintaining security and privacy data. All authors will have access to the final dataset only. The schedule of the enrolment, intervention, and assessment is shown in Fig. 2.

**Fig. 2 Fig2:**
[figure not shown]
The schedule of enrolment, interventions, and assessments

### Interventions

For the CKC and OKC exercise groups, the participants will perform an eight-week individualized home exercise with a minimum of three sessions per week [7]. Each session lasts about 30 min, including 10 min of walking as a warm up session before ending with quadriceps and hamstring stretch as a cool-down session [26–28]. Daily paracetamol (PCM) 3000 mg [24] will be provided by the Hospital USM orthopedic doctor to the participants in all three groups. However, the consumption of PCM is not compulsory, rather depends on each participant's needs. The PCM consumption will be recorded in the exercise diary that is provided. In addition, participants will be contacted through telephone calls and WhatsApp messages three times a week to encourage the participants to adhere to the exercises prescribed [7, 29, 30].

#### The open kinetic chain (OKC) exercise program

For the OKC exercise group, participants will perform the following exercises three times a week (Fig. 3):

**Fig. 3 Fig3:**
[figure not shown]
Open kinetic chain exercise program

1) Straight leg raising in lying position;

2) Knee extension in sitting position;

3) Hip abduction in lying position;

4) Hip adduction in lying position.

#### The closed kinetic chain (CKC) exercise program

For the CKC exercise group, participants will perform the following exercises three times a week (Fig. 4):

**Fig. 4 Fig4:**
[figure not shown]
Closed kinetic chain exercise program

1) Terminal end knee extension in standing (maximum 15° of knee flexion) [31];

2) Wall slide (semi squat);

3) Forward step up and down;

4) Side step up and down;

For both OKC and CKC groups, participants will perform all exercises for ten repetitions three times a week, for 8 weeks. Following that, if they consistently obtain less than three on the VAS scale [32], they are encouraged to increase the intensity of the exercise by increasing the number of sets with the same repetitions for each exercise.

#### Control group

All the participants will receive the usual care that includes health education about clinical manifestations, risk factors, diagnosis, treatment, and nursing care for knee OA. However, only the participants in the control group will be given the printed materials of clinical education. Furthermore, the control group will not be exposed to any information related to exercise programs [7]. After completing the trial, the participants in the control group will receive either CKC or OKC exercises depending on their preference.

### Measures

#### Descriptive data

Baseline data about participants’ age, gender, dominant leg, medical history, and medication history will be obtained through the questionnaires. The height (m) and weight (kg) of the participants will be measured with a digital medical scale (Seca 769, Hamburg, Germany). The body fat percentage will be measured by the Tanita Machine (TBF-410, Tanita Corporation, Tokyo, Japan). The leg length of the participants will be measured from the anterior superior iliac spine to the tip of the medial malleolus by using a measuring tape. Dominant feet will be identified by asking the participants which leg is used to kick a ball [33]. All the measurements of leg length, height, body weight, and percentage of body fat will be recorded whereas body mass (BMI) will be calculated.

### Primary outcomes

#### Pain

Pain intensity will be assessed using the (VAS) [32]. It is a reliable, valid, and responsive tool, and frequently used as an outcome measure for pain [32]. It consists of a bidirectional 10 cm straight line, where 0 cm is “no pain,” and 10 cm is “worst imaginable pain,” located at either end of the line [32]. Participants will be asked to choose a number that best represents their pain level. The VAS scoring will be recorded at the baseline assessment, after every exercise session throughout the 8-week intervention, and lastly at the end of the intervention program.

#### Functional disability

The Western Ontario and McMaster Universities Arthritis Index (WOMAC) Likert version 3.1 will be used to assess functional disability [31, 34]. The WOMAC includes 24 questions. Each question will be scored using five response options ranging from 0: none, 1: mild, 2: moderate, 3: severe, to 4: extreme [31, 34]. WOMAC is designed to assess the patients’ pain perception, stiffness, and disability. The scores will be summed within the three domains, giving a total score for pain (range: 0–20), stiffness (range: 0–8), and disability (range: 0–68) [31]. Higher scores indicate greater severity across the three domains [31, 34]. The Malay version of the WOMAC (M-WOMAC) will be used in this study to better cater to the local cultural background and language spoken in the Malaysian population [35]. Based on a survey that was conducted to test the reliability and validity of the M-WOMAC among 61 women aged 45–65 years in Malaysia, the Cronbach’s alpha of 0.976 showed that the M-WOMAC was valid and reliable to be used among the local population with knee OA [35].

#### Quality of life

The Osteoarthritis Knee and Hip Quality of Life (OAKHQOL) was developed to measure the quality of life, specifically among patients with hip and knee OA [36]. The Malay version of OAKHQOL (M-OAKHQOL) will be used in the present study because its cultural and language suitability for the Malaysian population [37]. Abdul Kadir et al. [37] reported that the M-OAKHQOL is a valid and reliable instrument to assess the health-related quality of life of knee OA patients in the Malaysian population with Cronbach’s alpha values that ranged from 0.865 to 0.933. The questionnaire consists of 31 items that assess the physical activity (10 items), mental health (eight items), pain (four items), social support (three items), and social functioning (three items) as well as three additional items for relationship, sexual activity, and professional life. These three additional items are meant to be used separately [37], and they will be included in this RCT. Each of the items will be rated on a scale of 0 to 10. The final score is the mean score of all the items. All the mean scores will be added together to generate a scale of 0 (best possible QOL) to 100 (worst possible QOL) [38].

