**Method:**

A total of 66 individuals with painful early knee OA, aged 50 years and above, with body mass index (BMI) between 18.9kg/m^2^ and 29.9 kg/m^2^ in Kelantan, Malaysia, will be recruited in this study. Participants will be randomly allocated into three different groups, either the OKC, CKC, or control groups. All three groups will attend an individual session with a physiotherapist. The participants in the OKC and CKC groups will perform the exercises three times weekly for 8 weeks at their home. The control group will receive education about clinical manifestations, risk factors, diagnosis, treatment, and nursing care for knee via printed materials. The primary outcomes include self-reported pain scores (visual analog scale), disability scores (Western Ontario and McMaster Universities Arthritis Index), and quality of life scores (Osteoarthritis Knee and Hip Quality of Life). Secondary outcomes include lower limb biomechanics during gait and sit-to-stand as well as isokinetic knee strength. The outcomes will be measured before and after the intervention.

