### Statistical analysis

Data will be entered and analyzed using SPSS version 25 (IBM Corp., Armonk, NY, USA). Only the data from the participants who have completed at least 75% of the study intervention will be analyzed. Data from drop outs will not be included in the analysis. Descriptive data will be reported as a mean ± standard deviation. Two-way ANOVA will be used to test the within- and across- group comparison of the VAS, WOMAC, and OAKHQOL scores, and isokinetic knee muscle strength, as well as lower limb biomechanics during gait and STS. The level of significance is set at a *p*-value < 0.05. A least significant difference (LSD) post hoc test will be conducted following any significant differences from the two-way ANOVA test.

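### The scoring rule for the OAKHQOL, a primary outcome, is inconsistent and cannot give the 0 to 100 scale it states

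*Protocol article*

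**What the plan says.** All of the scoring text is in the protocol article under Primary outcomes, Quality of life.

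- Structure: "The questionnaire consists of 31 items that assess the physical activity (10 items), mental health (eight items), pain (four items"; the list continues with "social support (three items), and social functioning (three items) as well as three additional items".
- Item range: "Each of the items will be rated on a scale of 0 to 10".
- The three extra items (relationship, sexual activity, professional life): "These three additional items are meant to be used separately [37], and they will be included in this RCT".
- Score, one sentence: "The final score is the mean score of all the items".
- Score, next sentence: "All the mean scores will be added together to generate a scale of 0 (best possible QOL) to 100 (worst possible QOL".

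No multiplication or normalisation step is given, and no other section defines the score. The Abstract lists "quality of life scores (Osteoarthritis Knee and Hip Quality of Life" among the primary outcomes. The Statistical analysis section carries the score into the test: "Two-way ANOVA will be used to test the within- and across- group comparison of the VAS, WOMAC, and OAKHQOL scores".

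**The concern.** Two consecutive sentences describe the final score, one as a mean over items and the other as a sum of means. The second attaches a range that neither operation appears able to produce. The text also leaves open whether 28 or 31 items count.

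Two things are at stake. First, values on a 0–10, 0–50 or 0–80 range would be read against anchors of 0 and 100. Second, an analyst could follow either sentence, or either item set, and reach different scores for a primary outcome. Because the choice is not fixed, it could be made after the data are seen.

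**Working it through.** **Inputs (Quality of life section).** Five domains of 10, 8, 4, 3 and 3 items, three additional items, each item 0 to 10.

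**Item count.** 10 + 8 + 4 + 3 + 3 = 28, and 28 + 3 = 31. This reproduces the stated 31.

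**Attempt to reproduce the stated 0–100 range.** A mean of 0–10 items has maximum 10, and a sum of k such means has maximum 10k.

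| Reading | Maximum | Score if every item is 5 |
|---|---|---|
| Mean of all items (28 or 31) | 10 | 5 |
| Sum of five domain means | 5 × 10 = 50 | 25 |
| Five domain means + one mean of the three extra items | 6 × 10 = 60 | 30 |
| Five domain means + three extra items singly | 8 × 10 = 80 | 40 |
| Raw sum, 28 items | 280 | 140 |
| Raw sum, 31 items | 310 | 155 |

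None gives 100. Adding 0–10 means would need exactly ten of them (100 / 10), and the text describes five to eight components. Multiplying a mean by 10 does give 0–100, but the text states no such step and speaks of adding.

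**Are the two sentences equivalent up to scale?** Under an item mean, a domain with k items has weight k/31 or k/28. Under a sum of five domain means, each domain has weight 1/5.

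| Domain | Item mean, 31 | Item mean, 28 | Sum of five means |
|---|---|---|---|
| Physical activity (10) | 32.3% | 35.7% | 20% |
| Mental health (8) | 25.8% | 28.6% | 20% |
| Pain (4) | 12.9% | 14.3% | 20% |
| Social support (3) | 9.7% | 10.7% | 20% |
| Social functioning (3) | 9.7% | 10.7% | 20% |

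The weights differ, so one score is not a linear rescaling of the other.

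**Illustration (assumed change, not from the protocol).** Suppose the 10 physical and 4 pain items each change by 2 points and nothing else moves. On a common 0–100 scale:

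- 31-item mean: 2 × 14 / 31 × 10 = 9.0
- 28-item mean: 2 × 14 / 28 × 10 = 10.0
- Equal domains: (2 + 2) / 5 × 10 = 8.0

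Unscaled, the sum of five domain means changes by 4 on a 0–50 range. The illustration has no variance and no test, so it shows only that the estimate depends on the rule.

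**The case against.** The two sentences can be read as successive steps: average items within each domain, then combine the averages. The plural in the second sentence supports this, since a single mean leaves nothing to add. The extra items may likewise be included only in the sense of being administered and reported on their own, in which case the 0–80 reading goes against the text. Both readings are fair. They narrow the problem but do not remove it: the combined score still ends at 50, and the sentence that averages every item still conflicts with separate use of three of them.

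A reader might infer that the quality-of-life results will be wrong or uninterpretable. The protocol does not support that. If the weighting is the same, scores on 0–10, 0–50 and 0–100 are linear rescalings; ANOVA p-values, group ranking and standardised effects do not change, and all three arms are affected alike. Nor is a changed test result shown: the weights differ, but there are no data from which to compute a test.

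Equal domain weighting is not an error in itself. Under it, one item of a three-item domain counts (1/3)/(1/10) = 3.33 times as much as a physical activity item, which is a legitimate choice if it is declared.

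It might also be inferred that results would be mis-scaled against other studies, or that item direction is wrong. The article gives no comparison figure and shows no direction error, and the scoring source it cites is not available here.

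The practical damage is limited in other ways too. The sample size rests on VAS and WOMAC. The Discussion gives clinically relevant changes for pain, WOMAC function and the knee adduction moment but none for OAKHQOL. Questionnaires are kept as hard copy, so items can be rescored.

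**Conclusion.** The point holds as an inconsistent and arithmetically impossible scoring rule for a primary outcome. The stated range is 0–100; the stated operations reach 10, 50, 60 or 80. Whether three of the 31 items enter the score is unresolved.

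The part that can affect inference is the weighting: physical activity counts for 32.3% or 35.7% under the item mean and 20% under the sum of five domain means. The scale error alone affects labelling and interpretation, not p-values. The score is best described as ambiguous and open to misreporting.

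This rests only on the item counts and item range in the article. It is a rule stated wrongly rather than detail left to an analysis plan, so the possible existence of such a plan does not answer it.

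**What to change.** Before analysis, replace the two scoring sentences with one rule that yields 0–100. One workable version:

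- Each domain score = mean of its items × 10 (0–100).
- The single pre-specified primary quality-of-life score = mean of the five domain scores (0–100). This equals twice the sum of the five domain means (2 × 50 = 100), so it keeps equal domain weights, and the protocol should say so.
- The three additional items stay out of the total and are reported separately.
- The individual domain scores are secondary. Making all five primary would turn one quality-of-life test into five, in a plan that already tests three primary outcomes at p < 0.05 with LSD post hoc comparisons.
- Delete the sentence about adding the means.

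If the sponsor prefers the 28-item mean × 10, that also gives 0–100; what matters is that one rule is named. The sponsor should confirm the choice against the scoring source it cites.

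The cost is two rewritten sentences and the scoring syntax. No new data are needed, and the sample size is unaffected.

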### Secondary outcomes

#### Lower limb biomechanics during gait and STS

To capture the biomechanical variable, infrared cameras with three-dimensional (3D) motion capture and analysis system will be used. Kinetic data will be collected using the force platform (Bertec, Ohio, USA) to measure the ground reaction force and joint moments whereas the kinematic data will be collected by the infrared cameras at 100Hz using the Qualisys track manager software (Qualisys, Sweden) and V3D software (version 5, C-Motion, Gothenburg, Sweden). Both the kinematic and kinetic data of the lower limb will be analyzed during the gait and STS test [39]. STS is commonly used to assess the strength and balance of the lower extremities [39]. STS has been shown to have a great intra and inter-rater reliability (ICC, 0.89) among hip and knee OA patients [40].

#### Isokinetic knee strength

Isokinetic knee flexion/extension strength will be evaluated using Biodex Dynamometer (Biodex Medical System, Shirley, NY, USA). The data to be collected will include the peak torque and muscular power of the hamstring and quadriceps. The dynamometer and chair will be adjusted to the appropriate height and length of each participant. Then, belts will be strapped on the participants to stabilize their trunk, pelvis, and contralateral thigh. The quantification of knee flexion/extension strength will be performed at the angular velocity of 180°/s [41, 42]. The speed has been chosen because it is associated with a reduction in the friction between knee cartilage, knee irritation, and other symptoms during muscle strength measurement [41]. To complete the measurement, all participants will perform each test in flexion/extension motion as hard as they can for five repetitions per set and two sets for both legs [41, 43].

### Additional measures

#### Adverse event

As a co-intervention, daily oral nonsteroidal anti-inflammatory drugs (NSAIDs) in the form of PCM 3000 mg [24, 44, 45] are provided. However, the usage of the PCM is not compulsory. Participants can consume the PCM as per their needs and record the usage in the diary provided. The pain scale (VAS) will also be recorded in the diary during the intervention period for all three groups of participants. Any adverse event during the intervention will be recorded in the provided diary. The participants will also be reminded to inform the physiotherapist immediately if they faced any problem during the eight weeks of the exercise program. The contact number is stated on the consent form. If necessary, the physiotherapist will contact the medical supervisor and co-supervisors for further investigation or management.

#### Adherence

An exercise diary will be provided to each participant from both CKC and OKC groups to ensure their adherence to the prescribed exercise at home. Similarly, participants in the control group will also be given a diary to record their daily physical activities. Additionally, a telephone call or WhatsApp message will be performed three times weekly throughout the 8-week intervention period to encourage the participants to adhere to their exercise program at home and to keep track of any adverse effects [7, 30].

### Statistical analysis

Data will be entered and analyzed using SPSS version 25 (IBM Corp., Armonk, NY, USA). Only the data from the participants who have completed at least 75% of the study intervention will be analyzed. Data from drop outs will not be included in the analysis. Descriptive data will be reported as a mean ± standard deviation. Two-way ANOVA will be used to test the within- and across- group comparison of the VAS, WOMAC, and OAKHQOL scores, and isokinetic knee muscle strength, as well as lower limb biomechanics during gait and STS. The level of significance is set at a *p*-value < 0.05. A least significant difference (LSD) post hoc test will be conducted following any significant differences from the two-way ANOVA test.

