**Fig. 1 Fig1:**
[figure not shown]
Participant flow through the randomized controlled trial

All participants will be assigned randomly to one of the three groups (CKC, OKC, or control groups) by an independent researcher. The allocation numbers will be generated by the study supervisor using a computerized random sequence. The 66 numbers will be inserted in opaque and sealed envelopes until a participant picks an envelope. The participants will then be allocated to the group stated in the envelope. A sealed copy of the randomization code listing will be kept by the study supervisor, and it will not be revealed until the study completion. Additionally, two research team members are designated as outcome assessors for the pre-and post-intervention tests. They will also be blinded to the group allocation and the statistical analyses. Participants will be reminded not to reveal their group allocation to the assessors. The study procedure will follow the Declaration of the Helsinki as approved by the Human Research Ethics Committee at the Universiti Sains Malaysia (JEPeM code: USM/JEPeM/19100645). The protocol has been registered at clinicaltrial.gov (NCT04678609).

The printed information sheet that explains this study will be given to the potential participants together with the consent form. These forms will be produced in a bilingual format in both Malay and English to ensure that all participants understand the research procedure. Participants will give their consent to start the pre-test and intervention sessions by signing the form. The form will also be signed by a witness and the researcher.

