### Monitoring

The researcher will be responsible for monitoring all the subject enrollment, the reasons for dropping out, and the listing of all the adverse events to prepare all the relevant reports. The researcher will also arrange a follow-up appointment with the medical officer for any drop-out participants. Regular meetings will be held every 2 weeks between the study supervisor and researchers to monitor any adverse events from the exercise program and to ensure timely completion of participants’ recruitment. Close communication will be maintained between the assessors and researchers to monitor any problems that arise during the stages of data collection and intervention implementation. Lastly, the study supervisor will conduct monthly audits of the raw data collected, as well as the interventions in the clinical trial. Any protocol modifications that are required during the study period will be submitted to the Ethics Committee of the Universiti Sains Malaysia for approval before further implementation.

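### The only stated analysis is restricted to participants who complete at least 75% of the intervention and do not withdraw, so it no longer compares the randomised groups and can be biased.

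*Protocol article*

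**What the plan says.** Three places in the protocol article together fix the analysis set.

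- Statistical analysis: "Only the data from the participants who have completed at least 75% of the study intervention will be analyzed", followed by "Data from drop outs will not be included in the analysis".
- Recruitment of participants: eligible people are "considered as drop-outs if they request to withdraw due to any reasons or if they are unable to complete 75% of the intervention program". Low adherence by itself therefore makes someone a drop-out.
- Trial design: "All participants will be assigned randomly to one of the three groups (CKC, OKC, or control groups) by an independent researcher". Both exclusion criteria operate after this step.

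The arms differ in what 75% could refer to. Under Interventions, the exercise groups have an "eight-week individualized home exercise with a minimum of three sessions per week". Under Control group, "the control group will not be exposed to any information related to exercise programs"; that group receives usual care and printed education, and under Adherence it keeps a diary of daily physical activity.

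The article gives no analysis of all randomised participants, no sensitivity analysis and no method for missing outcomes. The Monitoring section does plan some contact with those who stop: "The researcher will also arrange a follow-up appointment with the medical officer for any drop-out participants".

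**The concern.** Randomisation makes the three groups of 22 comparable. It does not protect subsets chosen by how well participants adhered or whether they stayed. In a home exercise trial with pain among its primary outcomes, a link between adherence and pain response is plausible: someone whose knee hurts more may stop, and so may someone who feels better. Either way, those retained differ systematically from those allocated.

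Two features make this worse than ordinary loss to follow-up. First, the rule creates missing data: a participant who does half the sessions and attends the post-test is still excluded. Second, the adherence criterion has a countable meaning in two arms and none in the third, so the groups need not be filtered alike.

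The rule governs every listed outcome: VAS, WOMAC, OAKHQOL, isokinetic strength and biomechanics. Once outcomes of low adherers are left uncollected or unanalysed, the bias can be neither corrected nor bounded from the trial's own data. The word only in the rule makes this a stated choice and not a detail left to a fuller analysis plan.

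**Working it through.** **The plan's own figures.**

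- Sessions in the exercise arms: 8 weeks × 3 per week = 24 at minimum; 75% of 24 = 18. For control, no corresponding count is stated.
- Anticipated loss (Sample size calculation): 20% in every group. 18 × 1.2 = 21.6, rounded to the stated 22 per group. Dividing instead, 18 / 0.8 = 22.5, would give 23; the difference does not matter here. At 20% loss, 22 × 0.8 = 17.6 per group remain.

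**Model for the exclusion rule.** Take standardised outcome Y (higher is better) and adherence A as bivariate normal with correlation ρ and no true treatment effect. If the fraction d with the lowest adherence is removed, the mean outcome of those kept shifts by

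bias = ρ × φ(z_d) / (1 − d), where z_d is the d-quantile of the standard normal and φ its density.

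With d = 0.20, φ(z_d) = 0.28, so φ(z_d) / (1 − d) = 0.28 / 0.80 = 0.35. If the removal occurs in one exercise arm and not in control:

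- ρ = 0.3: 0.3 × 0.35 = 0.105 SD
- ρ = 0.5: 0.5 × 0.35 = 0.175 SD
- ρ = 0.7: 0.7 × 0.35 = 0.245 SD

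The 20% is the article's dropout rate. Applying it to one arm only, and the values of ρ, are assumptions.

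**Type I error.** This was simulated with 20,000 trials per scenario, 22 per arm before exclusion and no true effect, using a two-sided 5% t test of one exercise arm against control. Positive bias favours exercise.

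| Removed, exercise / control | ρ, exercise / control | Simulated bias (SD) | Rejection rate |
|---|---|---|---|
| 20% / 0% | 0.3 / – | 0.107 | 6.2% |
| 20% / 0% | 0.5 / – | 0.170 | 8.1% |
| 20% / 0% | 0.7 / – | 0.243 | 11.6% |
| 20% / 20% | 0.5 / 0 | 0.175 | 8.0% |
| 20% / 0% | 0 / – | 0.001 | 4.9% |
| 20% / 20% | 0.5 / 0.5 | 0.001 | 5.2% |
| 20% / 0% | -0.3 / – | -0.104 | 6.4% |
| 20% / 20% | 0 / 0.5 | -0.178 | 8.1% |

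The first three rows agree with the formula to within simulation error. The fourth shows that equal loss in both arms does not remove the bias if the reasons for loss differ. The next two show when it vanishes: exclusion unrelated to outcome, or the same in both arms. The last two show it reversed: exercisers who improve stop early, or only the control exclusions are related to outcome.

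These rates describe a single two-arm test, not the planned two-way ANOVA with LSD comparisons, so they indicate scale only.

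**The case against.** The strongest objection concerns direction and size. A reader might infer that the rule does bias the trial towards exercise. The documents do not support that. They state no direction, and the calculation gives zero or reversed bias under assumptions that cannot be excluded. For the comparison named in the primary aim, open against closed kinetic chain exercise, a bias towards exercise has no meaning.

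A reader might also infer that control keeps everyone. It does not: withdrawal for any reason counts in all arms, and pain or lack of benefit could prompt it in control. What 75% means in control is undefined, which is different from its never applying; that arm also has a physiotherapist session, visits, printed material and a diary.

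Two further figures are tempting but do not stand.

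- Calling 0.175 SD 35% of the planned effect (0.175 / 0.5) assumes that 0.5 is a standardised mean difference. The Sample size calculation names no metric. If it is the ANOVA effect size f, the largest pairwise difference is about 1.06 to 1.22 SD and the share is about 14 to 17%.
- The fall from 66 to 54 widens standard errors by √(66/54) = 1.106, about 11%, but the trial is powered on 18 per group, so that loss is already allowed for. It also needs equal loss in all arms; with loss in the exercise arms only, 17.6 + 17.6 + 22 = about 57 remain.

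Nor does the rule suppress safety information: Monitoring requires reasons for dropping out and all adverse events to be listed.

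These objections limit what can be said about the bias. They leave the analysis set itself undefended.

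**Conclusion.** The concern holds: the article fixes a completers-only analysis, defined after randomisation by adherence and withdrawal, and discards outcomes that could be measured. The comparison is no longer between the randomised groups and can be biased, plausibly in favour of exercise against control and in an unknown direction between the two exercise programmes.

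The illustrative size against control is a spurious benefit of about 0.10 to 0.25 SD. It rests on no true effect, 20% removed from an exercise arm only and an assumed correlation of 0.3 to 0.7. The full range of scenarios tried runs from about -0.2 SD through zero to about 0.25 SD, with two-sided type I error from about 5% to about 12%. An unknown direction is no reassurance, because the excluded data are what would be needed to judge it. The point should be settled before the data are analysed.

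**What to change.** - Make the primary analysis all randomised participants in their allocated group, whatever their adherence.
- For the analysis, define drop-out as consent withdrawn or outcome not obtainable. Completing under 75% should be reported as adherence, not treated as loss.
- Invite participants who stop exercising to the scheduled week-8 post-test with the blinded assessors. If they cannot attend, obtain the questionnaires as a minimum. The medical-officer appointment under Monitoring has no stated timing or blinding, so it should not replace the post-test. A telephone pain score differs in mode from the 10 cm line and should be flagged. Strength and biomechanics still require attendance.
- Handle outcomes that are truly missing with a likelihood-based mixed model or multiple imputation.
- Keep the 75% set as a supportive analysis only, and state what the threshold means for control.

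The cost is slightly more follow-up and analysis work, and the estimated effect may be smaller. No extra recruitment is needed, since 66 are already planned. The article reports recruitment as still ongoing, and Monitoring provides for protocol changes to go to the ethics committee.
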